**PRIMARY:**

**CLINICAL PHASE:** III

**US IND NUMBER:** 9030

SITE:

INSTITUTIONAL REVIEW BOARD/ETHICS REVIEW COMMITTEE:

Summary of Changes

PRIMARY REASON FOR THIS AMENDMENT:

To clarify guidance criteria used to determine vaccine-relatedness of an adverse event. This change was previously reported in a protocol clarification letter dated 22-Sep-2010.

Sections impacted:

- Table 3-2 in section 3.4.6 was updated to move "possibly related" from the, "No, there is not a reasonable possibility of vaccine relationship", category and placed into the, "Yes, there is a reasonable possibility of vaccine relationship", category.

OTHER CHANGES INCLUDED IN THE AMENDMENT:

No other changes were made.

Table of Contents

Summary of Changes [2](#__RefHeading___Toc274236453)

PRIMARY REASON FOR THIS AMENDMENT: [2](#__RefHeading___Toc274236454)

OTHER CHANGES INCLUDED IN THE AMENDMENT: [2](#__RefHeading___Toc274236455)

1. SUMMARY [7](#__RefHeading___Toc274236456)

# 1. SUMMARY

## 1.1 Title

Long Term Follow-up Study of Safety, Immunogenicity, and Effectiveness of GARDASIL™ (Human Papillomavirus [Types 6, 11, 16, 18] Recombinant Vaccine) in Mid-Adult Women—The FUTURE III (Females United to Unilaterally Reduce Endo/Ecto Cervical Cancer) Study

## 1.2 Indication for Long term Follow-Up

HPV type-specific effectiveness endpoints will be collected by active surveillance of Pap abnormalities, biopsy and EEC specimens, and definitive therapy specimens using the clinic and investigators in Bogota, Colombia with all specimens tested as in Protocol 019 base study.

## 1.3 Summary of Rationale

Results of the Phase III studies have demonstrated that GARDASIL™ is highly efficacious in preventing HPV 6-, HPV 11-, HPV 16-, and HPV 18-related CIN, AIS, cervical cancer (via CIN 2/3 and AIS), VIN, VaIN, condylomata acuminata, vulvar cancer (via VIN 2/3), and vaginal cancer (via VaIN 2/3) in the group that received GARDASIL™ compared to the placebo group in subjects who were not infected with the relevant HPV type at the start of the study. This long term follow-up study is being conducted to assess the safety, immunogenicity, and effectiveness in the population of women who were vaccinated at 24-45 years of age through 10 years following vaccination Dose 1 (among GARDASIL™ recipients in the base study); and those vaccinated at 29-50 years of age through 5 years following vaccination Dose 1 (among placebo recipients in the base study).

Colombia was selected to perform this study because of the high numbers of study participants recruited from Bogota, and the commitment of both the investigators and the study participants to the study. The investigators also have experience in performing longitudinal studies and in motivating women to maintain adherence to the visit schedule.

## 1.4 Summary of Study Design

This Long Term Follow-up (LTFU) is a safety, immunogenicity, and effectiveness observational study. All subjects will sign an informed consent prior to initiation of any study procedure. Subjects will have been enrolled in the Protocol 019 base study in Colombia. Approximately 1,600 healthy women who meet the eligibility criteria will be invited to participate. The age of the women at the time of vaccination Dose 1 will range from 24 to 45 years of age among GARDASIL™ recipients in the base study and 29 to 50 years of age among placebo recipients in the base study.

HPV-related analyses will include: HPV type-specific PCR-based assays to determine the causal HPV type within a clinical lesion (such as a genital wart or a CIN2+ lesion).

The study will have general guidelines for referral of subjects for colposcopy and biopsy during the follow-up period. All biopsy specimens will also undergo HPV DNA analysis using Thinsection PCR. All biopsies will be analyzed at the central laboratory designated by the SPONSOR. The diagnoses provided by the lab will be used for routine management of subjects. However, the diagnoses provided by the lab will not represent the official diagnoses for study purposes. The slides will subsequently be reviewed by an Independent Pathology Panel; the consensus diagnosis of the Independent Pathology Panel will represent the final diagnosis for study purposes.

## 1.5 Sample

The study will enroll ~1,600 subjects who were enrolled in the Protocol 019 base study in Colombia.

• Cohort 1: ~800 of whom were vaccinated with GARDASIL™ at the beginning of the base study and

• Cohort 2: ~800 of whom were vaccinated with GARDASIL™ during the 019-10 extension (i.e., after the conclusion of the base study).

## 1.6 Dosage/Dosage Form, Route, and Dose Regimen

No vaccination will be provided in the long term follow-up.

## 1.7 Study Flow Chart

| Event/Test | Contact and Obtain Consent | Years following Base Study Day 1 visit (window for each visit is ± 6 months) | | |
| --- | --- | --- | --- | --- |
| 6 | 8 | 10 |
| Obtain informed consent | x |  |  |  |
| Review inclusion/exclusion criteria |  | x |  |  |
| Provide Participant Identification Card |  | x |  |  |
| Collect medical/gynecologic history † |  | x | x | x |
| Perform physical exam |  | x | x | x |
| Inspect external genital areas for warts/lesions‡ |  | x | x | x |
| Perform pelvic exam |  | x | x | x |
| Perform **optional** tests, as necessary§ |  | (x) | (x) | (x) |
| Perform Pap test (ThinPrep™) for cytology || |  | x | x | x |
| Inspect vaginal area for warts/lesions‡ |  | x | x | x |
| Perform bimanual exams |  | x | x | x |
| Collect blood (serum) for anti-HPV |  | x | x | x |
| Document clinical follow-up for safety ¶ |  | x | x | x |
| **Procedures must be conducted in the order provided within the study flow chart.**  Contact and consent may be obtained any time prior to procedures at Year 6 visit (including the day of year 6 visit). Visits for Year 6, Year 8 and Year 10 will be calculated from Day 1 of original study and visit window for each visit is +/- 6 months of actual time point.  † History will be updated as needed at these visits and at unscheduled visits.  ‡ The external genital wart/lesion exam must be conducted in 2 parts in order to limit contamination between anatomical areas. The external portion of the exam including vulvar, labia, perineum, perianal and other external areas will be performed prior to the pelvic exam. The vaginal portion of the wart/lesion inspection will be performed after the pelvic exam and all specimen collection is completed.  § HSV Culture may be performed if indicated. Vaginal pH, wet mount, whiff test, and KOH may be performed at the investigator's discretion.  || Cytology for Pap test to be performed by central laboratory selected by SPONSOR.  ¶ Serious adverse experiences, as defined in Section 3.4 will be collected for all subjects throughout the extension phase. All reports of pregnancy will be reported to the SPONSOR and followed to outcome. | | | | |

# 2. CORE PROTOCOL

## 2.1 Objectives and Hypotheses

The purpose of this extension is to observe the long term effectiveness of quadrivalent HPV (qHPV) vaccine, GARDASIL™.

### 2.1.1 Primary Safety

Objective: To observationally describe the general safety of a 3-dose regimen of GARDASIL™ [Human Papillomavirus (Types 6, 11, 16, 18) Recombinant Vaccine] in women 24 to 50 years of age during a period of 5 to 10 years following vaccine Dose 1 by describing vaccine- or study procedure-related SAEs, SAEs resulting in death and pre-specified medical conditions, and pregnancy follow-up outcomes.

Hypothesis: No hypothesis relating to safety will be tested.

### 2.1.2 Immunogenicity

Objective: To evaluate the kinetics and age-dependence of anti-HPV 6, 11, 16, and 18 responses following a 3-dose regimen of GARDASIL™ at approximately 6, 8, and 10 years after vaccination Dose 1 among subjects from the qHPV vaccine group of the base study and approximately 1, 3, and 5 years after vaccination Dose 1 among subjects from the placebo group of the base study.

Hypothesis: No hypothesis relating to immunogenicity will be tested.

### 2.1.3 Effectiveness

Objective: To observationally describe the incidence of HPV 6/11/16/18‑related genital warts or cervical dysplasia, and of HPV 16/18-related CIN2+ (Cervical Intraepithelial Neoplasia [CIN] grades 2 or 3, cervical Adenocarcinoma in Situ [AIS], and cervical cancer) 6, 8 and 10 years following administration of GARDASIL™ in 24 to 45 year-old women; and 1, 3, and 5 years following administration of GARDASIL™ in 29 to 50 year-old women.

HPV type replacement will also be observationally described. The incidence of non-HPV 6/11/16/18‑related genital warts or cervical dysplasia, and of non-HPV 16/18-related CIN2+ (Cervical Intraepithelial Neoplasia [CIN] grades 2 or 3, cervical Adenocarcinoma in Situ [AIS], and cervical cancer) in 6, 8, and 10 years following administration of GARDASIL™ in 24 to 45 year-old women; and at 1, 3 and 5 years following administration of GARDASIL™ in 29 to 50 year-old women in Colombia. The HPV types that will be studied are those studied in the base study, specifically HPV 31/33/35/39/45/51/52/56/58/59 and for all high grade lesions due to any non-vaccine type [1]. By way of background, the biological behavior of HPV makes replacement by non-vaccine genotypes a remote possibility according to presentations by both Eduardo Franco and Joakim Dillner at the recent EUROGIN meeting (Monte Carlo, Monaco, (Session DE 1, Vaccination, page 21, Thursday, 18 February 2010, <http://www.eurogin.com/2010/finalprogram.pdf>). Both presentations are in keeping with a summary by [name] in [2] (page 202). The biological characteristics of HPV do not lend themselves to type replacement. Namely, HPV uses human polymerase which produces very few mutations to facilitate natural selection, and infection with HPV is characterized by multiple HPV types, which is inconsistent with viral competition – a necessary feature for type replacement.

Hypothesis: No hypothesis relating to effectiveness will be tested.

## 2.2 Subject/Patient Inclusion Criteria

Subject was enrolled in Protocol 019 in Colombia and received at least 1 injection of GARDASIL™ or placebo.

Subject is aware of duration of study and is willing to participate through Year 10 of the study.

## 2.3 Subject/Patient Exclusion Criteria

Subject has any condition which in the opinion of the investigator might interfere with the evaluation of the study objectives.

Subject is unable to give informed consent.

Subject is concurrently enrolled in a clinical study or studies that involve or would interfere with the collection of cervical specimens.

## 2.4 Study Design and Duration

### 2.4.1 Summary of Study Design

Approximately 1,600 healthy women, previously enrolled in Protocol 019 (the base study) and/or Protocol 019-10 in Colombia, will sign an informed consent prior to initiation of any study procedure. The women were 24 to 45 years of age when enrolled in the base study. During the base study at Day 1, subjects were stratified by age into 2 groups: those 24 to 34 years of age and those 35 to 45 years of age. Stratification accomplished balanced allocation within each stratum. In Colombia, approximately 800 subjects were vaccinated with GARDASIL™ during the base study at Day 1 and approximately 800 base study placebo recipients were vaccinated with GARDASIL™ at the end of the base study at approximately Year 5 in accordance with Protocol 019-10.

Safety data following administration of GARDASIL™ were collected on all study subjects within the context of Protocol 019 base study and Protocol 019-10 extension. Investigator-reported serious adverse event data as well as pregnancy outcomes will be collected within the context of this study (Protocol 019-20). The response of the immune system to the vaccine will be measured with a multiplex, competitive Luminex Immunoassay (anti-HPV 6, 11, 16, and 18 cLIA) and other serological assays. The PCR assays used to identify effectiveness endpoints are described in Section 3.3.4. The composition and operation of the blinded Independent Pathology Panel as well as the Panels roles and responsibilities are described in Section 3.3.7.2. The pathology endpoints will be determined by the Independent Pathology Panel, as in the base study.

### 2.4.2 Treatment Plan

No study vaccinations will occur within the context of Protocol 019-20.

## 2.5 List of Effectiveness/Immunogenicity Measurements

### 2.5.1 Immunogenicity Measurements

Serum will be analyzed to assess long term kinetics of immune responses and to explore the relationship between long term immune response and breakthrough disease. Immunogenicity endpoints are:

- Serum geometric mean titers (GMTs)
- Seropositivity rates to HPV 6, 11, 16, and 18

### 2.5.2 Effectiveness Measurements

**External Genital Warts or Cervical Dysplasia related to HPV 6, 11, 16, or 18:**

A subject will be considered to have a case of external genital warts or cervical dysplasia, related to HPV 6, 11, 16, or 18 during the follow-up period if she has the following:

- On an individual biopsy or excised tissue, a consensus by the Independent Pathology Panel diagnosis of condyloma acuminata (genital warts), or on an individual biopsy, ECC, LEEP, or Conization (cold knife/laser) specimen a consensus by the Independent Pathology Panel diagnosis of CIN 1, CIN 2, CIN 3, cervical adenocarcinoma in situ (AIS), or cervical cancer

AND

- Detection of HPV 6, 11, 16, 18 by Thinsection PCR in an adjacent section from the same tissue block.

**Cervical Intraepithelial Neoplasia Grades 2 or 3 (CIN 2+), Adenocarcinoma in Situ (AIS), and/or Cervical Cancer related to HPV 16 or 18:**

A subject will be considered to have a case of CIN 2+, AIS, and/or cervical cancer related to HPV 16 or 18 during the follow-up period if she has the following:

- On an individual biopsy, ECC, LEEP, or Conization (cold knife/laser) specimen, a consensus by the Independent Pathology Panel diagnosis of CIN 2, CIN 3, AIS, or cervical cancer

AND

- Detection of HPV 16 or 18 by Thinsection PCR in an adjacent section from the same tissue block.

### 2.5.3 HPV Type-Specific Replacement Measurements

**External Genital Warts or Cervical Dysplasia related to a specific non-vaccine HPV Type:**

A subject will be considered to have a case of external genital warts or cervical dysplasia related to a specific non-vaccine HPV type during the follow-up period if she has the following:

- On an individual biopsy or excised tissue, a consensus by the Independent Pathology Panel diagnosis of condyloma acuminata (genital warts), or on an individual biopsy, ECC, LEEP, or Conization (cold knife/laser) specimen a consensus by the Independent Pathology Panel diagnosis of CIN 1, CIN 2, CIN 3, cervical adenocarcinoma in situ (AIS), or cervical cancer

AND

- Detection of the relevant (from any of HPV types 31, 33, 35, 39, 45, 51, 52, 56, 58, or 59) HPV type by Thinsection PCR in an adjacent section from the same tissue block.

**CIN 2+, AIS, or Cervical Cancer related to a specific non-HPV 16/18 Type:**

A subject will be considered to have a case of CIN2+, AIS, and/or cervical cancer related to a specific non-vaccine HPV 16/18 type during the follow-up period if she has the following:

- On an individual biopsy, ECC, LEEP, or Conization (cold knife/laser) specimen, a consensus by the Independent Pathology Panel diagnosis of CIN 2, CIN 3, AIS, or cervical cancer

AND

- Detection of the relevant (from any of HPV types 31, 33, 35, 39, 45, 51, 52, 56, 58, or 59) HPV type by Thinsection PCR in an adjacent section from the same tissue block.

## 2.6 List of Safety Measurements

The following safety measurements will be collected:

- Serious Adverse Experiences (SAEs) (as defined in the detailed protocol) judged by the study investigator to be possibly, probably, or definitely related to prior administration of GARDASIL™
- SAEs (as defined in the detailed protocol) judged by the study investigator to be possibly, probably, or definitely related to a study procedure
- Death of a study subject

Safety outcomes as requested by regulatory agencies for each subject who has consented to this LTFU study and pregnancy outcome will also be collected during the follow-up period. Specific disorders will include **but are not limited to** incident cases of: systemic lupus erythematosus, rheumatoid arthritis, Guillain-Barre syndrome, acute disseminated encephalomyelitis and multiple sclerosis.

## 2.7 Statistical Analysis Plan Summary

In the absence of a control group in the LTFU study, it is not possible to perform analyses of efficacy. Instead, effectiveness will be measured in terms of incidence rates of disease, with analyses performed periodically until the end of the follow-up in Protocol 019-20. Three (3) analyses are planned, corresponding to the time when all participating subjects have completed each of the scheduled visits at Years 6, 8, and 10 relative to the base study Day 1. All subjects who received GARDASIL™ within the context of Protocols 019 base study or the 019-10 extension from the participating sites in Colombia will contribute to the effectiveness analyses. At each analysis time point, the cumulative and current (for the current interval) number of cases for each effectiveness endpoint will be counted by analytical cohort. Incidence rates based on accrued person-years of follow-up will be estimated together with a corresponding 95% confidence interval.

As an aid to interpretation, incidence rates observed during the LTFU study will be put in context with corresponding incidence rates observed during the base study to provide an assessment of vaccine effectiveness. If any other new data becomes available during the LTFU which provides relevant information for this study population, from Merck studies or the published literature, that will also be used to contextualize the incidence rates that will be observed during the LTFU study. All LTFU analyses will be specific to time since vaccination, so will be presented separately for Cohort 1 and Cohort 2. Cohort 1 includes subjects vaccinated with GARDASIL™ on Day 1 in the base study. Cohort 2 subjects were allocated to receive placebo during the base study and can be enrolled in the long term follow-up extension following receipt on GARDASIL™ in the first extension (Protocol 019-10).

Exploratory analyses may be done to assess the expected continued protection against recurrent infection in women who were seropositive and PCR negative to the relevant HPV type in the vaccine. Sensitivity analyses may be done to study expected *vs.* observed cases of disease due to recurrent HPV types.

The primary analysis approach for Cohort 1 will be per-protocol-efficacy (PPE), as defined during the base study. To be eligible for this population, subjects must (i) have received 3 doses of GARDASIL™ within 1 year, and (ii) have no protocol violations. Subjects will be considered cases related to a given HPV type provided the subject was negative to the respective HPV type by serology and PCR prior to vaccination (i.e., during the base study) and PCR negative through Month 7. For purposes of endpoint definition, only the Pathology Panel diagnosis will be considered. Supportive analyses will be done for the group naïve to the relevant HPV type (HNRT) and full analysis set (FAS). The HNRT population consists of all subjects who received at least 1 vaccination and were seronegative and PCR negative to the relevant type prior to vaccination. The FAS population includes all vaccinated subjects, regardless of HPV status. Subjects who were cases of the relevant endpoint during the main study will not be included in the LTFU analyses of that endpoint.

The base study PPE population definition can not be applied to Cohort 2 subjects due to absence of HPV serology and PCR status information on Cohort 2 subjects at the time immediately before injection of vaccine Dose 1, and absence of HPV PCR status at "Month 7", i.e., at 1-month post vaccine Dose 3. Therefore, the analysis on Cohort 2 subjects will be done on the FAS population.

The sample size for the effectiveness and immunogenicity components of the LTFU study is fixed by the number of Protocol 019 base study and 019-10 study participants from Colombia who are eligible and willing to participate in the LTFU study. There are approximately 800 subjects in each of Cohorts 1 and 2 in the participating sites in Protocol 019-20 who will contribute extension study data. Given this relatively small sample size, it is important to note that the expected number of endpoint cases that can potentially be observed over the LTFU period is low. For example, the incidence rate of HPV 16/18-related CIN2/3 in the per-protocol placebo group during the base study was 0.1 per 100 person-years. Table 2-1 illustrates incidence rate estimates and confidence intervals for the indicated numbers of cases that can potentially be observed during the LTFU period. It is clear that in many cases, the confidence intervals do not exclude the placebo incidence rate of 0.1.

Table 2-1

Example Incidence Rates for Numbers of Cases Observed During
Long-Term Follow-Up Period (Cohort 1 Subjects)

| Cumulative cases observed from start of LTFU | At 10 years from vaccination  Incidence/100 PY (95% CI) | |
| --- | --- | --- |
| 0 | 0 | (0.00, 0.08) |
| 1 | 0.02 | (0.00, 0.12) |
| 2 | 0.04 | (0.01, 0.15) |
| 3 | 0.06 | (0.01, 0.18) |
| Rate calculations assume full follow-up was obtained from 800 subjects in Cohort 1, to the indicated time points.  LTFU = Long Term Follow-up; PY = Patient years; CI = confidence interval | | |

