#### 3.5.5.1 Statistical Methods for Assessment of Effectiveness

Effectiveness will be assessed by computing cohort-specific incidences during the LTFU study as shown in Figure 3-1 and these LTFU incidences will be put into context against the incidences observed during the base study as summarized in Table 3-4. The cumulative incidence probabilities (or percents) based on non-parametric life-table methods, not the incidence rate (per 100 person-years), will be the primary metric that will be used for computing the cumulative incidences that will be used in observationally assessing effectiveness as summarized in Table 3-4.

Cohort 1

- At the Year 6 time point, cumulative incidence from Day 1 to Year 6 of HPV 6/11/16/18-related disease endpoints will be computed and reported. There are no corresponding 6-year cumulative incidences from the base study. Also at the Year 6 timepoint, cumulative incidences (of HPV 6/11/16/18-related disease endpoints) from Year 4 to Year 6, representing a 2-year incidence, will be computed and reported. This 2-year incidence will be evaluated in the context of the 2-year incidence from Day 1 to Year 2, and from Year 2 to Year 4, observed during the base study. Note that a 2-year period in the context of accumulating HPV 6/11/16/18-related disease endpoints is a very short time, the incidence is expected to be low, and the estimate of the cumulative incidence is not expected to have a high degree of precision.
- The continuing effectiveness of vaccination in Cohort 1 at the Year 8 time point will be assessed by evaluating the 4-year incidence in Cohort 1 from Years 4 to 8 (see Figure 3-1 and Table 3-4) in the context of Cohort 1's 4-year incidence from Day 1 to Year 4 during the base study. Similar 4-year incidences from Day 1 to Year 4 and from Years 4 to 8 are an indication of continuing vaccine effectiveness.
- The continuing effectiveness of vaccination in Cohort 1 at the Year 10 time point will be assessed by evaluating the 4-year incidence in Cohort 1 from Years 6 to 10 in the context of Cohort 1's 4-year incidence from Day 1 to Year 4 of the base study, and Cohort 1's 4-year incidence from Year 4 to Year 8. Similar 4-year incidences from Day 1 to Year 4, from Years 4 to 8, and from Years 6 to 10 are an indication of continuing vaccine effectiveness.

Cohort 2

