- At the Year 6 time point, Cohort 2 subjects would have had approximately only a 1-year follow-up relative to the date of their vaccine dose 1 injection. A 1-year follow-up time post-dose 1 is too short for the purpose of accumulating and observing HPV 6/11/16/18-related disease endpoints. No cumulative incidence summaries will be computed for Cohort 2 at the Year 6 time point.
- The effectiveness of vaccination in Cohort 2 at the Year 8 time point will be assessed by evaluating the incidence from vaccine dose 1 to Year 8, which for Cohort 2 represents a 3-year incidence post-dose 1 (see Figure 3-1 and Table 3-4), in the context of the GARDASIL™ group's 3-year incidence from Day 1 to Year 3 during the base study. The 3-year duration (instead of 4 years) for trying to capture and observe a HPV-related disease endpoint is a limitation of the Year 8 effectiveness assessment in Cohort 2.
- The effectiveness of vaccination in Cohort 2 at the Year 10 time point will be assessed by evaluating the 4-year incidence in Cohort 2 from Years 6 to 10 in the context of the GARDASIL group's 4-year incidence from Day 1 to Year 4 during the base study. Similar 4-year incidences from Day 1 to Year 4 in the base study GARDASIL™ group and from Years 6 to 10 in Cohort 2 is an indication of vaccine effectiveness in Cohort 2.

Table 3-4

Summary of Effectiveness Measures in the LTFU Study and the Corresponding
Incidence Measures in the Base Study
(By Analysis Time and Cohort)

| Analysis Time  Cohort | Incidence During LTFU Study | vs. | Incidence During Base Study |
| --- | --- | --- | --- |
| Year 6 |  |  |  |
| Cohort 1 | 6-year incidence (Day 1 to Year 6)  2-year incidence (Years 4 to 6) | vs.  vs. | N/A  2-year incidence† in Cohort 1§; 2-year incidence† in the Cohort 2║;  2-year incidence† in the Placebo group. |
| Year 8 |  |  |  |
| Cohort 1 | 8-year incidence (Day 1 to Year 8)  4-year incidence (Years 4 to 8) | vs.  vs. | N/A  4-year incidence‡ in Cohort 1§; 4-year incidence‡ in the Cohort 2║;  4-year incidence‡ in the Placebo group. |
| Cohort 2 | 3-year incidence (Years 5 to 8) | vs. | 3-year incidence¶ in Cohort 2║; 3-year incidence¶ in Cohort 1;  3-year incidence¶ in the GARDASIL™ group. |
| Year 10 |  |  |  |
| Cohort 1 | 10-year incidence (Day 1 to Year 10)  4-year incidence (Years 6 to 10) | vs.  vs. | N/A  4-year incidence‡ in Cohort 1§; 4-year incidence# in Cohort 1; 4-year incidence‡ in the Cohort 2║;  4-year incidence‡ in the Placebo group. |

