| Cohort 2 | 5-year incidence (Dose 1 to Year 10)  4-year incidence (Years 6 to 10) | vs.  vs. | N/A  4-year incidence‡ in Cohort 2║; 4-year incidence‡ in Cohort 1;  4-year incidence‡ in the GARDASIL™ group. |
| † Cumulative incidence from Day 1 to Year 2; and also cumulative incidence from Year 2 to Year 4.  ‡ Cumulative incidence from Day 1 to Year 4.  § Subjects from Colombia randomized to the GARDASIL™ group.  ║ Subjects from Colombia randomized to the placebo group.  ¶ Cumulative incidence from Day 1 to Year 3.  # Cumulative incidence from Years 4 to 8.  LTFU = Long term follow-up; N/A = Not available. There is no corresponding incidence during the base study. | | | |

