#### 3.5.5.3 Statistical Methods for Assessment of Immunogenicity

The procedure for estimating geometric mean titers (GMTs) as described in Section 3.3.2 of the V501-019 SAP will be used. GMTs and corresponding 95% confidence intervals of HPV (6, 11, 16, and 18) will be summarized for the time points indicated in Table 3-5.

Table 3-5

Summary of Time Points Post-Vaccine Dose 1 For Which HPV (6, 11, 16, and 18) Titers Will Be Available from the Base Study and LTFU Study

| Cohort | Time from Vaccine Dose 1 (in Months) | | | | | | | | |
| --- | --- | --- | --- | --- | --- | --- | --- | --- | --- |
| 7 | 12 | 24 | 36 | 48 | 60 | 72 | 96 | 120 |
| GARDASIL™ Group (Base study) † | + | + | + | + | + |  |  |  |  |
| Cohort 1 (LTFU study)† | + | + | + | + | + |  | + | + | + |
| Cohort 2 (LTFU study) |  | + |  | + |  | + |  |  |  |
| + indicates that HPV (6, 11, 16, and 18) titers will be available corresponding to the indicated time point in the indicated cohort at the end of the LTFU study.  † Cohort 1 includes subjects enrolled and vaccinated with GARDASIL™ on Day 1 in the base study who continued into LTFU.  LTFU = Long term follow-up. | | | | | | | | | |

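### The exclusion of base-study cases in Section 2.7 conflicts with the planned Day 1 to Year 6, 8 and 10 incidences and, read literally, understates them in the supportive full analysis set

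*Protocol*

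**What the plan says.** Section 2.7, after defining the per-protocol efficacy (PPE), HPV-naïve (HNRT) and full analysis (FAS) populations, adds: "Subjects who were cases of the relevant endpoint during the main study will not be included in the LTFU analyses of that endpoint". The sentence names no window and no population.

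Section 3.5.5.1 makes life-table incidence the main measure: "The cumulative incidence probabilities (or percents) based on non-parametric life-table methods, not the incidence rate (per 100 person-years), will be the primary metric". For Cohort 1 at the Year 6 analysis it says that "cumulative incidence from Day 1 to Year 6 of HPV 6/11/16/18-related disease endpoints will be computed and reported". Table 3-4 places three such measures in its column for incidence during the LTFU study: "6-year incidence (Day 1 to Year 6", "8-year incidence (Day 1 to Year 8" and "10-year incidence (Day 1 to Year 10" (each closes its bracket in the table). The comparator for all three is given as not available.

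On who belongs to Cohort 1, the Table 3-4 footnote reads "Subjects from Colombia randomized to the GARDASIL™ group". Section 3.5.7 agrees, and Section 2.7 says that all Colombian recipients of the vaccine contribute to the effectiveness analyses. The footnote to Table 3-5, which concerns antibody titres, describes Cohort 1 as women vaccinated "on Day 1 in the base study who continued into LTFU".

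Section 3.5 says that no separate analysis plan will follow, so this text is the plan.

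**The concern.** Dropping women who are already cases gives the right risk set for a window that opens at Year 4 or later: a first event cannot happen again. It does not suit a curve that opens on Day 1, because Years 0 to 4 of that curve are the base study and its events are the very women the rule removes. The curve is then zero at Year 4 by construction, whatever happened.

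Two analysts could follow this protocol in good faith, one applying Section 2.7 and the other applying the ordinary meaning of a life table from Day 1, and report different 6-, 8- and 10-year incidences. The version that applies the exclusion can only be equal or lower, which flatters the vaccine.

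**Working it through.** **Inputs.** From Table 3-6, Colombia cohort, GARDASIL arm, cumulative to Year 4:

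| Endpoint | FAS cases | FAS incidence | PPE cases |
| --- | --- | --- | --- |
| HPV 6/11/16/18 CIN or external genital lesion (composite) | 18 | 2.32% | 0 |
| HPV 16/18 CIN 2/3 or worse | 10 | 1.32% | 0 |
| HPV 6/11 external genital lesion | 3 | 0.39% | 0 |

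The FAS composite at Year 2 is 12 cases, 1.53%. I take the table's composite as a stand-in for the LTFU endpoint of genital warts or cervical dysplasia in Section 2.5.2; the two labels are not identical.

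**Reproducing the plan's figures.** 18 / 0.0232 = 776 women effectively at risk, consistent with about 800. A log-log 95% interval on 2.32% with that n is 1.47 to 3.66, against the printed 1.47 to 3.65. In Table 2-1, exact Poisson limits on 800 × 6 = 4,800 person-years give upper bounds of 0.077, 0.116, 0.151 and 0.183 per 100 person-years for 0, 1, 2 and 3 cases, which match its four rows. Person-time of 4, 5 or 10 years per woman does not match. Table 2-1 therefore counts Years 4 to 10 only.

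**Formula.** With F(a–b) the probability of becoming a case between Years a and b among women who are not yet cases at Year a:

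F(0–T) = 1 − [1 − F(0–4)] × [1 − F(4–T)]

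Under the literal rule F(0–4) is set to 0, so F(0–T) collapses to F(4–T). With base-study cases kept, F(0–4) is the Table 3-6 value.

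**Assumption.** The hazard after Year 4 is not in the documents. I let it run from 0 to 1 times the FAS hazard of Years 0 to 4. At the upper end, F(4–T) = 1 − [1 − F(0–4)]^((T−4)/4). For the composite at Year 10 this is 1 − 0.9768^1.5 = 3.46% under the rule, and 1 − 0.9768^2.5 = 5.70% with base-study cases kept.

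| FAS, Cohort 1 | Literal rule | Base-study cases kept |
| --- | --- | --- |
| Composite, Day 1 to Year 6 | 0 to 1.17% | 2.32 to 3.46% |
| Composite, Day 1 to Year 8 | 0 to 2.32% | 2.32 to 4.59% |
| Composite, Day 1 to Year 10 | 0 to 3.46% | 2.32 to 5.70% |
| HPV 16/18 CIN 2/3 or worse, Day 1 to Year 10 | 0 to 1.97% | 1.32 to 3.27% |
| HPV 6/11 external genital lesion, Day 1 to Year 10 | 0 to 0.58% | 0.39 to 0.97% |

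The absolute shortfall is F(0–4) × [1 − F(4–T)]. For the composite at Year 10 it lies between 2.32 × (1 − 0.0346) = 2.24 and 2.32 percentage points, so it hardly depends on the assumed hazard.

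**One scenario inside the range.** If the Years 2 to 4 hazard continues, each 2-year step is 1 − 0.9768 / 0.9847 = 0.802%. Then F(4–10) = 1 − (1 − 0.00802)³ = 2.39% under the rule, and 1 − 0.9768 × (1 − 0.00802)³ = 4.65% with base-study cases kept.

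**PPE.** F(0–4) = 0 in Table 3-6 for all three endpoints, so both readings give the same result. No HNRT counts are printed, so no HNRT figure can be computed.

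**The case against.** The strongest reply is that little of importance moves. The primary Cohort 1 analysis is PPE, and its Day 1 curve is zero to Year 4 under either reading. The Day 1 rows have no comparator, and no hypothesis is tested. Continuing effectiveness is judged on the Years 4 to 8 and 6 to 10 windows, where dropping earlier cases is correct. The FAS cases that would be lost are already printed in Table 3-6. Table 2-1 counts cases only from the start of LTFU, which suggests that the authors had new cases in mind when they wrote the rule. All of this stands, and it limits the reach of the point. It does not reconcile the two instructions: the rule has no window limit, and Table 3-4 lists the Day 1 incidences as LTFU measures.

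Some stronger readings are tempting, and the documents do not support them:

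- A reader might infer that the study's main 10-year result is biased. It is not: the zero PPE count rules that out for the exclusion.
- A reader might infer that the HNRT estimate is understated as well. It may be, but no HNRT case is reported.
- A reader might take the FAS incidence to be halved. That is one scenario, resting on six cases between Years 2 and 4 extended over six more years. The ratio depends on the assumed hazard; the absolute shortfall barely does.
- A reader might infer that Cohort 1 has two rival definitions for effectiveness. Sections 2.7 and 3.5.7 and the Table 3-4 footnote agree on all Colombian recipients. The narrower wording belongs to the immunogenicity table. Because the Table 3-4 footnote mark is attached only to the base-study column, a clarifying clause is still worthwhile.

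**Conclusion.** The conflict is real, and nothing in the protocol resolves it. Applied literally, Section 2.7 turns the Cohort 1 Day 1 to Year 6, 8 and 10 incidences into incidences from Year 4 under the wrong label. In the FAS, up to 18 composite cases, 10 HPV 16/18 CIN 2/3-or-worse cases and 3 HPV 6/11 external genital lesion cases would be lost, and the 10-year composite would be about 2.2 to 2.3 percentage points too low.

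This rests on Table 3-6, on the stated range for the later hazard, and on the women who were base-study cases otherwise being in the analysis set; the rule itself removes fewer if some of them do not enrol. The primary PPE result, the windows that start at Year 4 or 6, and the Cohort 2 windows are not affected. Should-fix.

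**What to change.** Two sentences, ideally settled before the data are frozen for the Year 6 analysis:

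1. In Section 2.7, limit the exclusion to windows that start once base-study follow-up has ended, and list them: Years 4 to 6, 4 to 8 and 6 to 10 in Cohort 1; the dose 1 and Years 6 to 10 windows in Cohort 2.
2. In Section 3.5.5.1, state that the Day 1 life tables count base-study cases as events and include every Colombian GARDASIL recipient in the relevant population, censored at her last evaluable visit, whether or not she continued into LTFU.

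The first sentence could also say that a woman who became a case between Years 4 and 6 is not at risk in the Years 6 to 10 window, since the present rule mentions only main-study cases.

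No new data are needed. The cost is a less favourable supportive FAS figure; the PPE figures stay as they are.
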